All interventional components are delivered by a Psychologist under the supervision of a senior Clinical Psychologist & Neuropsychologist. The full intervention is delivered over 12 weeks, inclusive of 10, 1-hour individual sessions (child and parent attends) and a separate parent and peer psychoeducational group session during each block (i.e. during the fatigue and cognitive intervention blocks). The group sessions reinforce the same psychoeducational components of individual sessions and are primarily to facilitate peer support. The cognitive rehabilitation-only intervention is delivered in a 6-week block consisting of 6 individual sessions (child and parent attends) and a parent and peer group session. Psychoeducational webinars for each block of cognitive fatigue and cognitive rehabilitation are provided to the child’s teacher/Special Educational Needs Co-ordinator (SENCo) to enhance systemic support and maximise generalisation of strategies. The intervention is delivered hierarchically with cognitive fatigue management introduced first (in the full intervention), followed by cognitive rehabilitation strategies with consideration to developmental stage of the child. The programme content and concepts (e.g., PQRST, chunking, pacing) per session are consistent across age groups, but the delivery (e.g., wording, supporting images, and consolidation activities) is adapted by age. Degree of involvement of an adult in intervention activities can be adapted according to the child’s level of development and independence.

The intervention can be delivered in face-to-face or remote format depending on participant preference. Meta-analysis
^
30
^ and review
^
31
^ of similar remote skills-based neuropsychological interventions for young people with diverse neurological conditions have recently found remotely delivered interventions have high levels of feasibility and acceptability without compromise to fidelity and efficacy. They also have the advantage of greater geographical reach and access for families who may otherwise be unable to participate
^
15,
32
^. Criteria for discontinuing the intervention includes patient request, disease relapse requiring urgent medical treatment, and where the participant becomes ineligible based on the eligibility criteria.

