Figure 1: Study Flowchart):

1. Fatigue measuresa. Primary outcome measure: Goal Based Outcome (GBO) for management of cognitive fatigue - parent & child
^
36
^
b. Secondary outcome measures: Multidimensional Fatigue Scale – parent and child
^
37
^, individual daily fatigue analogue scale (child), % school attendance (from school report)2. Cognitive measuresa. Primary outcome measure: GBO for management of cognitive difficulty – parent and child
^
36
^.b. Secondary outcome measures: Behaviour Rating Inventory of Executive Function – second edition (BRIEF-II) – parent and teacher, PedsQL Core + Brain Tumour Cognitive Problems module – child and parent
^
38
^, The Brief Illness Perceptions Questionnaire – child
^
39
^

These outcomes measures were selected due to their psychometric properties, suitability to the aims of strategy-based cognitive rehabilitation, and precedence and sensitivity to detecting change after rehabilitation interventions
^
22,
29,
40–
44
^. The MDFS was selected as an outcome measure for cognitive fatigue as it is the only fatigue measure that compartmentalises fatigue into subdomains. In our clinical experience of this population, sequelae of cognitive fatigue are often reflected across the domains of the MDFS (e.g., problems starting and finishing activities, feeling tired or napping after cognitive activities) but with higher scores within the cognitive domain. We will evaluate this profile in the final sample to inform if and how this measure should be used in an RCT. Where measures are protected by copyright (PedsQL Multidimensional Fatigue Scale, Core module, and Brain Tumour module, and the BRIEF-II) the appropriate license agreement has been obtained for use within the study.

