### Data processing and analyses

**
*Quantitative data*
**

A detailed statistical analysis plan will be produced prior to data analyses. All demographic, clinical, and neuropsychological assessment data will be summarised by group. Quantitative feasibility data will also be summarised for the sample. Quantitative data from TFA-questionnaires will also be used to compare and rank individual intervention sessions, the overall intervention, and compare to acceptability measures in the standard care arm. Means and standard deviations (or alternative as appropriate) for the satisfaction questionnaire will be described according to intervention arm.

Statistical analyses will mainly focus on change detected in the outcome measures (e.g., GBO, PedsQL, BRIEF-II). Means and standard deviations (or equivalent) will be described for the outcome measures for each group at each time point (baseline, week 6, and weeks 12–14), and compared using repeated measures ANOVA to address these two aspects of limited efficacy testing. The focus of the statistical analyses will be to estimate effect sizes (e.g., partial eta squared, Cohen’s d, or non-parametric equivalents as needed) for each measure. Effect sizes will then be ranked across the outcome measures to determine which is most sensitive to change to inform the future clinical trial. The 95% confidence intervals for the effect sizes will also be considered.

**
*Qualitative data*
**

Qualitative data generated by feasibility outcomes will be grouped into themes. Frequency rates for each theme will be calculated if this is appropriate. It will be used to accompany description of quantitative feasibility data.

The primary qualitative data will be generated by the TFA-informed interviews. This data will be analysed using thematic analysis
^
45
^, an analytic method that explores patterns and themes in qualitative data. Themes will be analysed according to the TFA. The final analyses will be shared with two participants to provide a member check of final themes and discussed with the Patient and Public Involvement Advisory Group.

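### Effect sizes are ranked across fatigue and cognitive measures together, with no term or contrast named, although the two constructs are treated in different numbers of arms and at different times

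*Protocol article*

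**What the plan says.** Under Study data and outcome measures (Preliminary outcome measures), the protocol lists two sets. The fatigue set has "Primary outcome measure: Goal Based Outcome (GBO) for management of cognitive fatigue - parent & child", followed by the Multidimensional Fatigue Scale, a daily fatigue analogue scale and school attendance. The cognitive set has "Primary outcome measure: GBO for management of cognitive difficulty – parent and child", followed by the BRIEF-II, the PedsQL Core and Brain Tumour Cognitive Problems module, and the Brief Illness Perceptions Questionnaire.

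Under Data processing and analyses, the outcome measures are to be "compared using repeated measures ANOVA to address these two aspects of limited efficacy testing". Descriptive statistics are given "for each group at each time point (baseline, week 6, and weeks 12–14"). The aim is to "estimate effect sizes (e.g., partial eta squared, Cohen’s d, or non-parametric equivalents as needed) for each measure". Then: "Effect sizes will then be ranked across the outcome measures to determine which is most sensitive to change". The same section adds: "The 95% confidence intervals for the effect sizes will also be considered".

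On treatment content, the Intervention section says: "The cognitive rehabilitation-only intervention is delivered in a 6-week block consisting of 6 individual sessions", with a group session in addition. This is Arm B. Arm A has the fatigue block first and the cognitive block second. Arm C is standard care.

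**The concern.** The purpose of the ranking is to learn how sensitive each instrument is to change. An effect size from a trial is not a property of the instrument alone. It also depends on how many of the compared children were treated for the construct, and on when they were treated relative to the visits.

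Here those two things differ between the sets. Cognition is treated in two arms of three: weeks 1-6 in Arm B and weeks 7-12 in Arm A. Fatigue is treated in one arm, in weeks 1-6. A list that crosses the sets can therefore place one measure above another for reasons that lie in the design. The tilt is in the expected effect sizes, so more children would not remove it.

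The ranking feeds objective 4, the choice of outcome measures for the larger trial. The arm to take forward is decided separately, under objective 2. A good fatigue measure could be passed over although Arm A goes forward.

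**Working it through.** **The plan's own figure.** The only relevant figure is the sample size: 3 arms × 12 = 36, which reproduces. No effect size, SD or power is stated.

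**Inputs from the protocol.** Three arms of 12; visits at baseline, week 6 and weeks 12-14; repeated measures ANOVA; fatigue block in Arm A first, cognitive block in Arm A second, cognitive block in Arm B in weeks 1-6.

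**Assumptions not in the protocol.** Every measure moves by the same d baseline SDs once its construct has been treated. Gains are kept. Arm B gives no fatigue benefit. d = 0.3 to 0.8, within-child correlation ρ = 0.5 to 0.7. The two measures being compared are simulated independently.

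**Cell means in units of d (baseline, week 6, weeks 12-14).**

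| | Arm A | Arm B | Arm C |
|---|---|---|---|
| Cognition | 0, 0, 1 | 0, 1, 1 | 0, 0, 0 |
| Fatigue | 0, 1, 1 | 0, 0, 0 | 0, 0, 0 |

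**Time effect, three visits.** SS = 3 × Σ(visit mean − grand mean)².
- Cognition: visit means 0, 1/3, 2/3, grand mean 1/3. SS = 3 × (1/9 + 0 + 1/9) = 0.667.
- Fatigue: visit means 0, 1/3, 1/3, grand mean 2/9. SS = 3 × (4/81 + 1/81 + 1/81) = 0.222.
- Ratio 3:1.

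**Group effect, three visits.** SS = 3 × Σ(arm mean − grand mean)².
- Cognition: arm means 1/3, 2/3, 0. SS = 3 × (0 + 1/9 + 1/9) = 0.667.
- Fatigue: arm means 2/3, 0, 0. SS = 3 × (16/81 + 4/81 + 4/81) = 0.889.
- Ratio 0.75:1, in favour of fatigue.

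**Group-by-time, three visits.** Total SS minus the two above.
- Cognition: total = 3 − 9 × (1/3)² = 2; 2 − 0.667 − 0.667 = 0.667.
- Fatigue: total = 2 − 9 × (2/9)² = 1.556; 1.556 − 0.222 − 0.889 = 0.444.
- Ratio 1.5:1.

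**Baseline to end only.** Changes by arm are (1, 1, 0) for cognition and (1, 0, 0) for fatigue. The squared mean changes are (2/3)² and (1/3)², so the time ratio is 4:1. The between-arm variance of the two patterns is identical, so group-by-time is exactly 1:1. Arm count alone therefore does not tilt the interaction. The 1.5:1 at three visits comes from the staggered cognitive block.

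**Population partial eta squared** at d = 0.5, ρ = 0.5: 12d²SS / [12d²SS + (1 − ρ) × 33 × (visits − 1)].
- Time, three visits: 2.0/35.0 = 0.057 for cognition; 0.667/33.667 = 0.020 for fatigue.
- Group-by-time, three visits: 0.057 for cognition; 1.333/34.333 = 0.039 for fatigue.
- Group-by-time, baseline to end: 1.0/17.5 = 0.057 for both.

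**Simulated ranking.** 20,000 trials per setting, 12 per arm, d = 0.3 to 0.8, ρ = 0.5 to 0.7. A fair comparison gives 50%. Cohen's d is the baseline-to-end change divided by the baseline SD.

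| Effect size ranked | Cognition outranks equally sensitive fatigue |
|---|---|
| Time, three visits | 60-88% |
| Group-by-time, three visits | 54-68% |
| Pre-post d pooled over all arms | 67-92% |
| Cohen's d, A and B versus C | 62-84% |
| Group-by-time, baseline to end | 50-51% |
| Cohen's d, A versus C | 50% |

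**Sensitivity to spillover of fatigue benefit into Arm B.**
- Half: fatigue visit means 0, 1/2, 1/2. Time SS = 3 × (1/9 + 1/36 + 1/36) = 0.5; ratio 0.667/0.5 = 1.33:1.
- Full: time SS 0.889; ratio 0.75:1, reversed.
- The three-visit interaction ratio does not shrink: 2.00:1 at half spillover, 1.50:1 at full. The baseline-to-end interaction ratio is 1.33:1 at half and 1:1 at full.

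**Sensitivity to fading.** If half of an early gain is lost by weeks 12-14 and there is no spillover, the A-versus-C change is 0.5d for fatigue and d for cognition. A contrast in which both constructs are treated is then no longer neutral.

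**The case against.** The strongest reply is that the protocol leaves the term and contrast to a later analysis plan, gives its effect sizes only as examples, and in objective 3 frames the comparison against standard care. Some permitted choices carry no tilt. This stands in part. A reader might infer that cognition measures will systematically rank higher, simply because two arms are treated instead of one. The documents do not support that: the direction depends on a term they do not name, the three-visit interaction excess comes from timing, and at 12 per arm any tilt is a tendency.

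It can also be said that the ranking may be meant within each set, since the sets are listed separately and objective 4 speaks of measures in the plural. That reading is possible, but the ranking sentence makes no such split. A reader should likewise not infer that the plan commits itself to one winning measure.

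The assumption of no fatigue benefit in Arm B is not given by the protocol, and the time-effect tilt depends on it. This stands, hence the spillover range.

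A further possible inference is that the ranking would put a fatigue measure into a trial of Arm B. That runs against the direction of the main tilt, and the Conclusions already ask that efficacy measures match the aims of the intervention. It is a reason to state the matching rule, not evidence of error.

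Confidence intervals answer imprecision only. They do not correct a difference in what the effect sizes are expected to be.

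**Conclusion.** The concern holds in a limited form. The protocol states a ranking across all outcome measures, without separating the sets and without fixing the term or contrast. The order can therefore reflect the treatment layout as well as the instruments. With equal sensitivity, lasting gains and no spillover, cognition measures are favoured on the three-visit time effect, less strongly on the three-visit interaction, and on effects pooled over Arms A and B. Other effect sizes that the text allows are neutral or favour fatigue. Larger claims, such as a bias present whatever analysis is chosen, go beyond the documents. The point affects how objective 4 is answered. It does not affect the feasibility and acceptability aims, and it is a cheap improvement.

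**What to change.** In Data processing and analyses, replace the ranking sentence with a rule in three parts, and carry it into the analysis plan:

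1. Rank fatigue measures only against each other and cognitive measures only against each other, using the sets already listed under Preliminary outcome measures.
2. Base each ranking on a contrast with standard care that is named in advance and in which the construct is treated: A versus C for fatigue, A and B versus C for cognition.
3. Choose the outcome for the definitive trial from the set that matches the arm taken forward.

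If any comparison across the sets is kept, use A versus C for both, and note that the blocks still differ in timing and in number of individual sessions (four in the first block and six in the second, Table 1).

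The change needs no new data, visits or children. The cost is that there is no single overall ranking. The split is also imperfect for general measures in the cognitive set, such as the PedsQL Core and the illness perceptions questionnaire, which fatigue management might also move; a sentence saying so is enough.

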### Sampling and sample size

Thirty-six participants in total will be recruited into the study via convenience sampling of the current and retrospective (past 48 months prior to study start date) patient pool from the Neuropsychology service. All children with a diagnosis of brain tumour under GOSH Neuro-Oncology medical care can be referred to the Neuropsychological service on a combination of prospective and bespoke protocols. Children treated curatively for high-grade solid tumours (including head and neck tumours with brain irradiation), or low-grade brain tumours with radiotherapy, are assessed at baseline, 2 years, and 5 years post treatment. Children with low-grade tumours without radiation are referred based on known risk factors for cognitive impairment (e.g., shunted hydrocephalus, midline tumours) and/or presenting cognitive concerns. All children treated for brain tumour remain under surveillance with the multidisciplinary team until they transition to adult services.

Participants will be recruited continually until the sample is reached. Continual recruitment involves offering the study to potential participants as they come through the clinical service systematically, and by searching the service database backwards systematically (in reverse order of assessments completed) over the past 48 months and applying the inclusion and exclusion criteria to invite potential participants. Priority will also be given in this order to patients who are either due to turn 18 years old, transition to another service, or would become ineligible for another reason within the next 6 months. All potential participants will be contacted initially by a member of their healthcare team via telephone, letter, patient messaging, or by discussion with their neuropsychology clinician on completion of their neuropsychological assessment. The GOSH neuro-oncology multidisciplinary team will be made aware of the study objectives, inclusion, and exclusion criteria and can inform potential participants of the study. Only trained and delegated members of the healthcare team can discuss the study in detail or provide Patient Information Sheets (PIS). The rationale for this sampling strategy is to maximise recruitment of a broad range of potential participants who meet the essential inclusion criteria to answer key questions of feasibility and acceptability in this population to inform the future RCT.

The justification for the sample size comes from the NIHR Research Design Service (RDS) London evidence for sample sizes for feasibility studies (
https://www.rds-london.nihr.ac.uk/resources/justify-sample-size-for-a-feasibility-study/) and associated evidence for estimating a standard deviation to power the future definitive trial. There is no formal way to power a standard deviation estimate which is a measure of variability, therefore various rules of thumb have been developed that the sample size for a feasibility trial should be between 24–50
^
46,
47
^. A sample size of 36 (12 participants per arm of the study) is further justified by the feasibility and the precision this provides in estimating the mean and the variance
^
46
^. This can then be used to calculate power for a more precise hypothesis for a definitive randomised controlled trial.

### Recruitment

Pre-screening will include screening potential participants according to the inclusion and exclusion criteria 1) on completion of prospective neuropsychological assessment, and 2) retrospectively over the 48 months prior to study date. Neuropsychological assessment reports and patient electronic records will be screened to determine if participants potentially meet the inclusion and exclusion criteria. This screening will be conducted by a member of the healthcare team within the neuropsychology service. Sources of identifiable information are the referrals record for neuropsychological assessment, electronic patient record system, and neuropsychological assessment reports. Potential participants' will only be approached by a member of the healthcare team initially. A comprehensive screening of inclusion and exclusion criteria will take place once potential participants consent to study inclusion. Participants will be advised to take a minimum of 24 hours to consider participation before giving consent. Participants may wish to take longer to decide, and the study will remain open to opt in to as long as they remain eligible and can complete the 14-week participation period within the timeframe of the study completion. Participants are not paid to participate in the study but will have access to a travel budget of £100 to compensate for travel expenses.

**
*Confidentiality*
**

All investigators and study site staff must comply with the requirements of the Data Protection Act 2018. A password protected Site Enrolment and Participant Log will be stored in duplicate on a secure GOSH Trust drive and encrypted external device and only accessible to members of the research team directly involved in recruitment, data quality control, and audit. The Site Enrolment and Participant Log will be stored in a separate location to the CRFs and other study data. Every participant will be allocated a unique Participant Identification Number (PID) on study entry. The PID consists of an unrelated random sequence of characters. The Site Enrolment and Participant Log will be the only document that will link the participants name and NHS number with the PID. At no point in presentations or publications of study data will individual patients be identified. Any direct quotes used will be anonymised and will not contain potentially identifiable information. Personal data will be stored for no longer than 12 months after study completion and will only be accessed where this is essential to the study.

**
*Study monitoring*
**

The Chief Investigator will be responsible for the day-to-day management of the study with support from the study management group. The study is a low risk non-CTIMP and does not require a data monitoring committee (DMC). A Trial Steering Committee (TSC) has been established to provide overall supervision for the study on behalf of the study's Sponsor and Funder and to ensure that it is conducted to the rigorous standards set out in the UK Policy Framework for Health and Social Care and the Guidelines for Good Clinical Practice. The conduct of the research will be subject to monitoring and auditing according to the Joint Research & Development Office for GOSH/University College London - Institute of Child Health standard research operating procedures.

**
*Risk and safety monitoring and reporting*
**

The NIHR ‘Decision Tree for Adverse Event Reporting – Non-CTIMPS’, including standard definitions of an Adverse Event (AE) and Serious Adverse Event (SAE) will guide study monitoring. It is highly unlikely that a serious adverse event/reaction would be attributable to this low-risk non-CTIMP trial. However, all AEs and SAEs will be documented in an Adverse Event Reporting log and CRF. Where an SAE occurs, this will be reported to the Sponsor within 24 hours. Participants will be notified of relevant events within 7 days or prior to their next study contact if this is sooner. If during any study activity a participant or their carer discloses risk or safeguarding concerns (i.e., their intention to harm themselves or others), the local GOSH Trust risk assessment and safeguarding policy will be immediately followed.

**
*Dissemination*
**

The NIHR and Success Charity will be acknowledged in any dissemination. A full report of the study findings will be submitted for publication within 2 years of study completion. The formal findings will be submitted to peer-reviewed scientific journals and, where possible, presented at relevant conferences and shared with relevant stakeholders. A lay summary of the findings will be co-produced with our PAG for dissemination amongst service-users, charities, and relevant social media. We aim to use the findings from this project to apply for funding for a multicentre RCT. Participants who request results from the CI will be provided with this information after the results of the study have been published.

Authors will be individually named on the final study report. Authors will have made a substantive intellectual contribution to the report and guided by The International Committee of Medical Journal Editors recommended authorship criteria:
https://www.icmje.org/recommendations/browse/roles-and-responsibilities/defining-the-role-of-authors-and-contributors.html.

